### Analyses

#### Description of incidence

Person-years at risk will be calculated as the interval between baseline and follow-up assessment, or the estimated time of onset of dementia, or the time of death, whichever occurs sooner. Age-specific incidence (with Poisson standard errors and 95% confidence intervals) will be estimated for each country, by gender and age in 5-year bands by dividing number of cases by number of person-years contributed in each age band. Dementia onset is assumed to be the midpoint between the last date when known to be dementia free and the first date of dementia diagnosis (either by survey ascertainment or clinical information). A similar procedure will be used to calculate stroke attack rates.

#### Hypothesis testing

We will use Cox's proportional hazards regression throughout to estimate risk associations. Informative censoring may occur through the competing risks of participants dying and becoming lost to follow-up in the interval between assessments. This problem is only rarely addressed in dementia cohort studies [53]. We will do so firstly by verbal autopsy interviews with key informants for all deceased persons, and secondly (in a sensitivity analysis) by using proportional subdistribution hazards regression [98] to account for informative censoring through explicit analysis of competing risks.

The ADMIXMAP program [99] will be used to model genetic admixture. In two-step analysis, estimates of individual admixture generated by ADMIXMAP are simply plugged into standard programs for statistical analysis. One-step analysis fits regression models for the effect of individual admixture and other risk factors (genetic or environmental) on disease risk. This allows for the uncertainty in estimation of individual admixture from the marker data, eliminating residual confounding by population stratification that may occur in a two-stage analysis using a small number of markers, and allows us to model haplotypes given unphased genotype data. For this study, ADMIXMAP will be extended to support Cox regression (regression algorithms are based on a GLM approach). We shall test for

1) effects of individual admixture on dementia, AD and other outcomes

2) effects of individual admixture on the slope of relationship of APOE to dementia.

3) effects of other environmental factors or genetic polymorphisms on dementia, again controlling for population stratification.

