### Interviews and data collection

#### Mortality

For those who died between baseline and follow-up (information ascertained on follow-up visit) we will complete a verbal autopsy interview with a co-resident, relative or other person well-placed to know the circumstances of death, using methods developed and validated by the 'Million Deaths' project for use in India [95,96] to identify underlying cause according to ICD10 criteria. The interview takes 30–45 minutes using structured questions and an open-ended narrative, with a symptom list to assist attribution. Cause of death is allocated by the consensus judgement of two physicians. The approach is valid for use up to three years post-mortem. We will also attempt to ascertain whether the participant had an onset of dementia before death, using the standard 10/66 informant assessment.

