### Methodological issues

Our one phase dementia diagnostic assessment has advantages over the two phase approach used in most previous dementia cohort studies [104]. Attrition is marked between the first and second phase [2]; participants with probable dementia are particularly likely to refuse, to move away or to die, leading to informative censoring. The problem is compounded when no random sample of screen negatives is selected for second phase assessment with the tacit assumption of perfect sensitivity for the screening measure [104-106].

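### Subdistribution-hazards regression is planned as a sensitivity analysis for informative censoring by death and loss to follow-up, but it corrects neither and shifts hazard ratios by construction

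*Protocol article*

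**What the plan says.** Under Analyses, Hypothesis testing, the protocol article fixes the main model: "We will use Cox's proportional hazards regression throughout to estimate risk associations". It then states the problem: "Informative censoring may occur through the competing risks of participants dying and becoming lost to follow-up in the interval between assessments".

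Two measures follow. The first acts on the dead only: "firstly by verbal autopsy interviews with key informants for all deceased persons". The Mortality section adds that "We will also attempt to ascertain whether the participant had an onset of dementia before death", using the study's informant assessment. The second, labelled a sensitivity analysis, is to proceed "by using proportional subdistribution hazards regression [98] to account for informative censoring through explicit analysis of competing risks".

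The article gives no other analytic measure for informative loss to follow-up. Footnote 1 of Table 2 assumes 15% non-response or non-traceability. Primary objective 5 is mainly aetiological: it asks whether cardiovascular risk factors, stroke and other exposures raise the risk of incident dementia and Alzheimer's disease. The first secondary objective studies cardiovascular risk factors and disease as determinants of mortality.

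**The concern.** A sensitivity analysis should tell the reader whether the main result survives the problem it is aimed at. This one is aimed at dependence between censoring and dementia onset, and the chosen model contains no term for that dependence.

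**Loss.** There are two ways to code it, and neither helps. Coded as a competing event, lost people stay in the risk set as if they could no longer develop dementia. Coded as ordinary censoring, loss is assumed to be non-informative, which is the assumption in question.

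**Death.** Death is a genuine competing event. The subdistribution hazard ratio describes the exposure's effect on the cumulative incidence of dementia in the presence of death. Part of that effect is the exposure's own effect on mortality, because people who die early cannot become cases. This is a legitimate quantity, but it answers a different question from the aetiological one and does not repair the Cox estimate.

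At stake is the reading of the comparison. For exposures that raise mortality, the subdistribution ratio lies below the Cox ratio whether or not censoring is informative. The article describes the model as accounting for informative censoring, so a reader could take the gap to mean that Cox was inflated. Informative loss would meanwhile remain unexamined.

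**Working it through.** **Inputs from Table 2 and its footnotes.** Dementia incidence is 0.0092 per year and mortality 6% per year. For the six Latin American centres the table gives 11,650 people free of dementia at baseline, 24,426 person-years, 2,072 deaths and 219 incident dementias. Follow-up is 2.5 to 3.5 years (Abstract). Exposure prevalences of 10% and 20% come from Table 3.

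**Assumed.** The document gives no hazard ratio of exposure on death. I use 1.5 to 3.

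**Reproducing the plan's figures.**
- Incident dementia: 24,426 × 0.0092 = 224.7, against 219 (within 3%).
- Deaths: N × (1 − exp(−0.06T)). With T = 3.5 years for Cuba, Dominican Republic and Venezuela (N = 6,250) and T = 3 years for Mexico, Peru and Argentina (N = 5,400), this is 1,183.8 + 889.5 = 2,073, against 2,072. The split of T is inferred from the table.
- Deaths per dementia case: 2,072 / 219 = 9.5. The competing event is much the commoner one.

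**Formula.** Take constant hazards, with λ for dementia and μ for death, independent of each other, so that the Cox (cause-specific) ratio equals the true one. Then

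F = λ/(λ+μ) × (1 − exp(−(λ+μ)T)), and subdistribution HR ≈ log(1−F₁)/log(1−F₀).

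The group hazards are set so that the population averages stay at 0.0092 and 0.06.

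**Worked case:** 20% exposed, T = 3, mortality HR 2. Here μ₀ = 0.06/1.2 = 0.05 and μ₁ = 0.10.
- True HR 1.0: λ = 0.0092 in both groups; F₀ = 0.02529, F₁ = 0.02353; ratio = 0.02382/0.02561 = 0.93.
- True HR 1.5: λ₀ = 0.0092/1.1 = 0.00836, λ₁ = 0.01255; F₀ = 0.02302, F₁ = 0.03194; ratio = 0.03246/0.02329 = 1.39.

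**Range, death as the only competing event, T = 3, 20% exposed:**

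| Mortality HR (assumed) | True HR 1.0 | True HR 1.5 |
|---|---|---|
| 1.0 | 1.00 | 1.50 |
| 1.5 | 0.96 | 1.44 |
| 2.0 | 0.93 | 1.39 |
| 3.0 | 0.88 | 1.32 |

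With 10% exposed the values at mortality HR 3 are 0.87 and 1.30. Follow-up of 2.5 or 3.5 years moves the entries by up to about 0.03.

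**When death really is informative.** A simulation added a shared frailty linking death and dementia (SD 1, assumed). At mortality HR 2 the net, cause-specific and subdistribution ratios were 1.48, 1.38 and 1.28; at 3 they were 1.47, 1.29 and 1.13. Taking the net ratio as the target, the subdistribution model moved further away from it.

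**The case against.** The strongest reply is that this is a secondary check, and much of that stands. Verbal autopsy comes first and tries to recover dementia before death directly. Cox remains the main model, so no primary estimate or test changes. Objective 5 also asks for population attributable fractions, for which effects on cumulative incidence have some relevance. With death as the only competing event the shifts are modest. At mortality HR 2, log(1.5/1.39) = 0.08, against a standard error of the log hazard ratio of about 1/√(219 × 0.2 × 0.8) = 0.17. That comparison reassures less than it seems to, because both models are fitted to the same data and the gap between them is systematic, not sampling noise.

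Three stronger readings are tempting, and the article does not support them:
- A reader might infer that lost participants will certainly be kept in the risk set as dementia-free. The text calls loss a competing risk but does not state how it will be coded. The point holds because neither coding corrects informative loss.
- A reader might cite the Methodological issues section, where "participants with probable dementia are particularly likely to refuse, to move away or to die, leading to informative censoring", as the plan's own account of loss in this cohort. That sentence concerns attrition between the phases of two-phase surveys, not three-year loss among people free of dementia at baseline.
- A reader might expect much larger shifts if loss were coded as competing and differed by exposure. The direction is right where loss is higher among the exposed, but the article gives no loss rates by exposure, so no size can be attached.

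The absence of censoring weights from a condensed article would not by itself be a finding. The finding is that the article assigns the task to a model that cannot perform it.

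**Conclusion.** The point holds as an error in the stated purpose of a sensitivity analysis. Subdistribution-hazards regression does not account for informative censoring by death or by loss, and loss should not be grouped with death as a competing risk. The primary Cox hazard ratios are not affected, and the plan does have another measure for the dead.

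The shift with death alone is about 4% at an assumed mortality HR of 1.5, 7% at 2 and 12% at 3 (3 years, 20% exposed, constant and independent hazards). It can make a null exposure look mildly protective. The mortality hazard ratios are assumptions; the incidence and mortality rates are the plan's.

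A reader might infer that the main results are biased or that the check will inevitably be misread. Neither follows: Cox is unchanged, and the article sets no rule for interpreting a difference between the two models. The correction is still worth making, because the check moves by construction and the assumed 15% loss is left without a working sensitivity analysis.

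**What to change.** 1. Keep the planned Cox model, described as cause-specific, for the aetiological hypotheses, and keep verbal autopsy for dementia before death.
2. Delete the statement that the subdistribution model accounts for informative censoring, and stop calling loss to follow-up a competing risk.
3. If the subdistribution model is reported, use death as the only competing event and label the result as an effect on cumulative incidence (absolute risk), not as a check on the Cox estimate.
4. Make the sensitivity analysis for loss a Cox model with inverse-probability-of-censoring weights built from baseline covariates already collected, together with simple bounds for dementia among the lost.

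This costs a change of wording, one extra weighted model and a bounding calculation, with no new data. The weights rely on measured predictors of loss, so they cannot remove dependence on unmeasured ones; the bounds are there for that reason.

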#### Power and sample size considerations

Power estimations were carried out using Stata 8.2 ssmenu command [100] for sample size and power calculations in complex studies with failure time outcomes (table 2). Pooling the data across the six Latin American centres yields the following power (Table 3) for identification of the following effect sizes for associations with incident dementia and stroke, assuming the following prevalences of risk exposure.

**Table 2 T2:** Incident dementia, stroke and all-cause mortality in centres participating in the follow-up study

Country	Baseline sample	Dementia at baseline	Free of dementia at baseline	Available for FU interview^1^	Person years	Deaths	Incident dementia^2^	Incident strokes
Cuba	3000	330	2670	1994	6730	509	55	45
DR	2000	220	1780	1329	4488	339	37	30
Venezuela	2000	200	1800	1345	4490	339	37	30
Mexico	2000	200	1800	1381	2906	295	30	25
Peru	2000	200	1800	1381	2906	295	30	25
Argentina	2000	200	1800	1381	2906	295	30	25
Sub-total^3^	13000	1350	11650	8811	24426	2072	219	180
China	2162	137	2025	1513	5105	366	42	30
TOTAL	15000	1300	11700	10324	29531	2438	261	210

1. assuming 6% annual mortality (GBD 2002 AMRO B mortality data, 65 and over), and 15% non-response/non-traceability.

2. annual incidence rate of 0.0092 for all those aged 65 and over, from consensus prevalence estimates for Latin America [19], using DISMOD to derive incidence from prevalence and survival.

3. These centres included fasting blood samples, which are lacking in China

**Table 3 T3:** Power to detect given effect sizes (HRs) for associations between exposures with a prevalence of 10% and 20%, for the outcomes of dementia and stroke.

Minimum Hazard Ratio to be detected	Power for detecting association with 10% exposure prevalence		Power for detecting an association with 20% exposure prevalence	
Outcome^1,2^	Dementia	Stroke	Dementia	Stroke

2.5	100%	99.8%	100%	100%
2.0	96.4%	90.9%	99.8%	98.8%
1.8	86.0%	75.8%	97.5%	92.8%
1.5	48.8%	39.3%	71.0%	59.5%

1. The power to detect associations with all-cause mortality approximates to 100% in each of these cells

2. As approximately 70% of dementia cases are categorised as AD, the power of detecting given associations with this outcome is very similar to that for stroke.

For the nested incident case-control study we estimate that 219 cases and 657 matched controls will be available. Given the matching, all analyses will be carried out using conditional logistic regression (Stata 8.2). For exposure prevalences ranging from 5% (lowest realistic estimate of prevalence for folate deficiency and subclinical hypothyroidism) to 40% (likely prevalence of vitamin B_12 _deficiency) such a comparison will have good (80%) to excellent (90%) power for detecting policy-relevant effects (Table 4).

**Table 4 T4:** Minimum detectable effect size (OR) for matched incident case-control comparison

**Exposure Prevalence Power**	**5%**	**10%**	**15%**	**40%**
80%	2.4	2.0	1.8	1.6
90%	2.7	2.2	2.0	1.7

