##### 1) Outcome – The diagnosis of dementia

Our previously published 10/66 dementia diagnosis algorithm [5] requires

(i) A structured clinical mental state interview, the Geriatric Mental State, which applies a computer algorithm (AGECAT)[74], identifying organicity (probable dementia), depression, anxiety and psychosis and,

(ii) A cognitive test battery comprising a) the Community Screening Instrument for Dementia (CSI'D') COGSCORE [75] (incorporating the CERAD animal naming verbal fluency task), and b) the modified CERAD 10 word list learning task with delayed recall [76] and

(iii) An informant interview the CSI'D' RELSCORE [75], for evidence of cognitive and functional decline

(iv) an extended informant interview, the History and Aetiology Schedule – Dementia Diagnosis and Subtype (HAS-DDS), a modification of the earlier HAS [77], providing more detailed information on onset and course of a possible dementia syndrome

v) The NEUROEX, a brief fully structured neurological assessment with objectified quantifiable measures of lateralising signs, parkinsonism, ataxia, apraxia and primitive 'release' reflexes [78,79].

(vi) Behavioural and Psychological symptoms of dementia (BPSD); assessed using an informant questionnaire, the Neuropsychiatric Inventory (NPI-Q) [80].

Final dementia diagnoses is made in two ways. The main dementia outcome is defined as those scoring above a cutpoint of predicted probability of DSM IV Dementia syndrome [81] from the logistic regression equation developed in the 10/66 international pilot study, using coefficients from the GMS, CSI-D and 10 word list learning tasks [5]. The second approach involves the direct application of research diagnostic criteria for DSM IV and for the following dementia subtype diagnoses; NINCDS-ADRDA Alzheimer's disease criteria [82], NINDS-AIREN vascular dementia criteria [83], and Lewy Body Dementia [84]. The clinical assessment identifies other prevalent conditions relevant to the differential diagnosis of dementia and dementia sub-type: psychosis, depression, anxiety disorder, alcoholism, epilepsy and stroke. Circularity in further validation of these diagnoses can only be avoided by focusing upon their predictive validity. Thus, a diagnosis of dementia should lead to further cognitive and functional decline, and not recovery.

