The 10/66 dementia diagnosis has been carefully validated across all of the cultures, and in each of the centres in which the population research is proceeding. While sensitivity (94%) and specificity (97% in high education controls and 94% in low education controls), against the gold standard of a local clinician's DSM IV diagnosis were both excellent, the false positive rate which varied between 1% and 10% across regions and levels of education can be expected to result in a higher prevalence of 10/66 dementia, compared with that of DSM IV dementia. DSMIV criteria are recognized to be relatively restrictive. Impairment is required in memory and other specified domains of function. Each of these must have progressed, and led to social or occupational impairment. The deficits should not be explained by delirium or other mental disorder. The aim with DSMIV (and other similar diagnostic criteria) was to define a progressive and relatively pervasive disorder with thresholds set high to maximize reliability between raters and centres. Clinically relevant dementia may therefore be prevalent beyond the confines of the narrowly defined DSM IV criterion. One of the few population-based studies to examine this issue directly, the Canadian Study of Health and Aging [107] reported a prevalence of 20.9% for those aged 65 and over according to clinical consensus compared with 13.7% according to DSM IV criterion. Mild cases, confirmed by clinicians, were selectively excluded by the DSM IV criterion. None of the DSM IV criteria are specifically required by the 10/66 probabilistic algorithm, which simply requires a profile of cognitive impairment on formal testing, informant reports of cognitive and functional decline, and findings on clinical interview that are consistent with a high probability of being a case. While the DSMIV algorithm identifies clear cut, severe and pervasive dementia cases, the 10/66 algorithm may be more relevant to establishing the true population burden of the dementia syndrome.

The catchment area sampling strategy enables us to foster links within each local community, improving response and facilitating possible follow-up. Community sensitisation proved to be essential to ensure a good response to the surveys. Prevalence estimates and other descriptive elements may not generalize beyond these and similar communities, but this is unlikely to lead to bias in estimates of association.

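### Table 2 pairs a 10–11% baseline dementia prevalence with an incidence of 0.0092 from another source; at 6% mortality the two are not plausibly consistent, so the 219 events probably do not describe the main (10/66) outcome

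*Protocol article*

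**What the plan says.** All places are in the protocol article.

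- **Power and sample size considerations, Table 2.** The six Latin American centres have 13,000 people at baseline, 1,350 with dementia and 11,650 free of it, 24,426 person-years and 219 incident cases. Baseline dementia is 11% in Cuba and the Dominican Republic and 10% in the other four. China is listed separately: 137 of 2,162 (6.3%) with dementia and 42 incident cases.
- **Table 2, footnote 1:** "assuming 6% annual mortality (GBD 2002 AMRO B mortality data, 65 and over), and 15% non-response/non-traceability".
- **Table 2, footnote 2:** "annual incidence rate of 0.0092 for all those aged 65 and over, from consensus prevalence estimates for Latin America", obtained by "using DISMOD to derive incidence from prevalence and survival". The consensus prevalence itself is not given, and neither dementia column names a case definition.
- **Outcome – The diagnosis of dementia:** "The main dementia outcome is defined as those scoring above a cutpoint of predicted probability of DSM IV Dementia syndrome". This is the 10/66 algorithm. Direct application of DSM-IV criteria is the second approach.
- **Methodological issues:** the algorithm's false-positive rate, 1% to 10% across regions and education levels, "can be expected to result in a higher prevalence of 10/66 dementia, compared with that of DSM IV dementia".
- **Catchment areas and sample registration** plans on a typical prevalence of 4.5%. **The casefinder study** expects about 90 cases in 2,000, which is also 4.5%.
- **New biochemical assays**, and the nested case-control paragraph before Table 4, start from 219 cases: 219 + 657 controls = 876 samples.

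**The concern.** DISMOD links incidence, prevalence and survival: given two, the third follows. An incidence obtained this way belongs to the prevalence that went in. Table 2 applies it to a cohort whose printed prevalence is 2.3 times the 4.5% used elsewhere in the article (10.4/4.5). If the baseline column counts cases by a broad definition and the incidence column by another, the table describes no single outcome.

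At stake is what the power section refers to. The 219 events feed the dementia columns of Table 3, the detectable odds ratios in Table 4 and the assay number. A reader cannot tell whether these concern the main 10/66 outcome. If they do, the event count is probably too low. If they concern a narrower definition, somewhat too many people leave the risk set at baseline.

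**Working it through.** **1. The plan's own count.** 24,426 × 0.0092 = 224.7, against 219 printed (2.6% apart). Persons available × years × 0.0092 gives the same picture: Cuba 1,994 × 3 × 0.0092 = 55.0 (printed 55) and China 1,513 × 3 × 0.0092 = 41.8 (printed 42). One rate was thus used for centres with 10–11% baseline dementia and for China at 6.3%.

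**2. Crude steady state (no population growth).** Prevalence odds = incidence × mean duration.
- Odds = 1,350/11,650 = 0.1159. Duration = 0.1159/0.0092 = 12.6 years.
- Mortality with dementia = 1/12.6 = 0.0794. Mortality without = (0.06 − 0.1038 × 0.0794)/0.8962 = 0.0578. Ratio = 1.37.
- At 4.5% prevalence: odds 0.0471, duration 5.1 years, mortality ratio 3.6.
- China at 6.3%: duration 7.4 years, mortality ratio 2.5. Nothing is odd there, and China lies outside the 219.

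**3. Age structure (assumed, not in the documents).** Stationary illness-death model from age 65 to 110, calibrated to crude mortality 0.06; mortality doubles every 8 years and incidence every 6; 0, 1 or 2% prevalent at 65.

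| Mortality ratio | Prevalence implied by 0.0092 (0 / 1 / 2% at 65) | Incidence matching 10.4% (1–2% at 65) |
|---|---|---|
| 1 | 6.6 / 7.5 / 8.4% | 0.012–0.013 |
| 1.5 | 5.2 / 6.0 / 6.8% | 0.015–0.017 |
| 2 | 4.3 / 5.0 / 5.7% | 0.018–0.020 |
| 3 | 3.3 / 3.8 / 4.4% | 0.023–0.024 |

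Other doubling times move the range to 6.0–8.9% at ratio 1 and 3.9–6.0% at ratio 2. About 10% is reached only if incidence does not rise with age and dementia carries no excess mortality.

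**4. Effect on counts.** Events scale as 219 × incidence/0.0092. At 0.012 this is about 285, and at 0.0243 about 580. Assays at 1:3 matching: 285 × 4 = 1,140 and 580 × 4 = 2,320, against 876.

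**5. Effect on Table 3.** Each printed power is turned into a noncentrality (two-sided 5% assumed) and multiplied by √(events/219).
- HR 1.5, 10% exposure, printed 48.8%: (1.96 − 0.03) × √(285/219) − 1.96 = 0.24, or 60%. With 580 events, 88%.
- HR 1.8, 10% exposure, printed 86.0%: 93% with 285 events and over 99% with 580.

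These are approximate. The Schoenfeld formula with 219 events does not reproduce Table 3 throughout (43.6% against 48.8% at HR 1.5; 86.8% against 96.4% at HR 2.0, both at 10% exposure).

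**6. False positives.** Take a true prevalence of 4.5% and the article's 94% sensitivity. Algorithm-positive prevalence is 0.045 × 0.94 + 0.955 × 0.06 = 10.0% at 94% specificity, and 5.2% to 13.8% over the 1–10% false-positive range.

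**The case against.** The strongest reply is step 6. With the article's own accuracy figures, 4.5% true dementia already yields about 10% algorithm-positive people. A 10–11% baseline and a true-disease incidence of 0.0092 can then both be right, and the article says openly that 10/66 prevalence will be higher. Feeding the raw 10/66 prevalence into DISMOD would treat stable false positives as disease with an onset. They are removed at baseline and need not return as incident cases, so 285–580 could overstate events. This stands as a limit on the size and on the remedy. It does not remove the point, because the explanation itself puts two case definitions in one table, unlabelled.

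Three stronger readings are tempting, and the documents do not support them:
- **That the figures cannot coexist.** On crude figures they can, with a 12.6-year duration and a mortality ratio of 1.37. A strict contradiction needs age structure or population growth, which the article does not give.
- **That the 219 are DSM-IV events.** Footnote 2 cites only a consensus prevalence and names no diagnostic criterion. That the 219 are not 10/66 events is an inference.
- **That the study is underpowered.** The likely error runs the other way. Even that direction is not fixed by the documents: the crude model with no excess mortality (duration 1/0.06 = 16.7 years) gives 0.1159/16.7 = 0.0070, about 165 events.

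It is also fair that the baseline surveys are nearly complete, so power no longer sets the sample, and that the assay number is stated as conditional on 219 cases.

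**Conclusion.** The point holds as an inconsistency of sources. Table 2's baseline prevalence and its incidence are not plausibly consistent at 6% mortality, and 0.0092 sits far better with a prevalence near 4.5% than with 10–11%. The 219 events, Tables 3 and 4 and the 876 assays are probably not the figures to expect for the main outcome.

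The likely error is an understatement, by a factor of about 1.3 to 2.7 (285–580 events) under a stationary population, the assumed age gradients, 1–2% prevalence at age 65, mortality ratios of 1 to 3 and no false positives. Because the last assumption is favourable to a high count, that range is an upper-end illustration and not a replacement figure. For power the error is conservative. The practical risks are an assay budget that is too small and a hazard ratio of 1.5 being treated as further out of reach than it is. If a narrower definition was meant, the loss is modest: at 4.5% prevalence the risk set would be 13,000 × 0.955 = 12,415 instead of 11,650, or 6.6% more. The correction is worth making but does not threaten the design.

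**What to change.** 1. In Table 2, name the case definition behind the baseline-dementia column and behind the incident-dementia column.
2. Keep the 219 as a conservative row labelled with the consensus definition. State the prevalence that went into DISMOD and use that same prevalence for the baseline column of the row.
3. Add a row for 10/66 dementia in the six Latin American centres, with incidence derived from the 10/66 baseline prevalence and the stated mortality. Show it as a range over the assumed mortality ratio and over the 1–10% false-positive rate under Methodological issues, so that stable false positives are not all counted as disease.
4. Carry both rows into Tables 3 and 4 and into the assay number.

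The cost is a re-run of DISMOD and of the power tables. If the 10/66 row is used to plan the nested study, the assay budget may have to grow or the 1:3 control ratio be looked at again. No change to data collection is needed.
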